### Study design

We will embed this study on women’s empowerment within the SCC Trial. The SCC Trial will recruit pregnant women and follow-up over 24 months of an expected 2840 mother–child dyad, from recruitment in early pregnancy until the child is 18 months of age. The intervention will run for 36 months, depending on the time of enrolment and gestation, and the age of the child.

## Methods

This study will use a mixed-methods approach with data gathered on women’s empowerment from participants in the SCC Trial. This protocol paper will adhere to the SPIRIT (Standard Protocol Items: Recommendations for Interventional Trials) and Tidier guidelines for clinical trial protocols^26–28^ to ensure rigour in protocol content.

### Study setting

We will conduct the study in two subdistricts of Sirajganj, Ullapara and Kamarkhanda, in northern Bangladesh (figure 2). Employment in Sirajganj is predominantly in agriculture (51 %), with 25% working in services and 23% in industry.^29^

**Figure 2 F2:**
[figure not shown]
Sirajganj, Bangladesh, Shonjibon Cash and Counselling study site.

### Eligibility criteria

All married women between 15 and 49 years, who are permanent residents of the study area and provide consent to participate and test positive with pregnancy urine test kit (Excel) (whose gestational age is ≤90 days), are eligible to participate in the SCC Trial.

### Intervention: Shonjibon^1^ Cash and Counselling Trial

A separate protocol paper provides details of the design of the SCC Trial.^12^ Briefly, the SCC Trial aims to assess the effectiveness of nutrition BCC (delivered via call centre counselling and specifically tailored mobile app) combined with unconditional cash transfers in reducing the prevalence of stunting (length for age<−2 Z) in children at 24 months. We will use a longitudinal cluster randomised controlled trial to determine the effectiveness of unconditional cash transfers and mobile BCC to reduce child undernutrition in Sirajganj district in northern Bangladesh, one of the poorest regions in the country according to the World Food Programme Poverty Maps.^30^ Both quantitative and qualitative approaches will be employed to address the study objectives.

The SCC Trial intervention arm receives (1) nutrition BCC delivered on a specially tailored app on a smartphone (audio, video and animation); (2) direct nutrition counselling from a call centre; and (3) unconditional cash transfer of 1000 Taka (US$12.50) received monthly via BKash mobile banking app. The control arm will receive a mobile phone and the current government of Bangladesh health and nutrition services. The participants in the control arm receive a mobile phone as the trial is interested in the effects of the messages, nutrition counselling and cash transfer delivered on a mobile platform, as opposed to the non-specific effects of a mobile phone.

### Study outcomes

The primary study outcome will be the difference in women’s empowerment scores in the intervention arm as compared with the control arm of the SCC Trial. Secondary study outcomes will include (1) control over income and economic resources, (2) input and decision-making power in nutrition and healthcare choices, and (3) experience and attitude towards IPV.

### Outcome measurements

The SCC trial will collect data across the main module of the Pro-WEAI (12 indicators) as well as the additional health and Pro-WEAI Nutrition and Health Module. However, six of the Pro-WEAI indicators are likely to be directly impacted by the SCC trial; therefore, we will develop a composite women’s empowerment indicator based on the following: (1) control over the use of income, (2) input in production decisions, (3) autonomy in income, (4) decision-making power about women and children’s health and nutrition, (5) respect among household members and (6) attitudes towards IPV (online supplemental appendix table 1). We will also measure women’s and family members’ perceived and lived experiences related to women empowerment qualitatively (online supplemental appendix table 1).

10.1136/bmjopen-2020-044263.supp1Supplementary data

Control over the use of income. We will measure control over the use of income by asking questions from Pro-WEAI; these questions are significant as the SCC Trial gives an unconditional cash transfer to the woman. Quantitative questions assess a woman’s input into decision making on all sources of household income. Qualitative interviews will explore local perceptions of intrahousehold harmony and communication skills, issues related to withdrawing the cash, and perceptions and experience of control and expenditure of the money.Input in productive decisions. These Pro-WEAI questions centre around input into household decision making on areas such as livelihood choices (activities the household participates in, such as agricultural activities, home gardens, etc), employment and household purchases.Autonomy in income. This includes a series of vignettes, validated by cognitive testing, using a series of hypothetical scenarios to assess motivation as to how income is used.Decision-making ability about health and nutrition choices. We will examine responses from the Pro-WEAI Nutrition and Health Module regarding confidence and participation in decisions about nutrition and infant feeding, as well as a range of issues affecting women and children, such as whether to consult a doctor when ill to dietary choices when pregnant.Respect among household members. Questions in this indicator pertain to a woman’s spouse or other household members on respect and trust within relationships, and level of comfort in disagreeing with household members.Intimate partner violence. Previous research in Bangladesh has found that cash transfers and BCC can reduce IPV.^8^ We will measure a woman’s attitude towards IPV using the Pro-WEAI as well as the direct experience of IPV using the questions from the Violence Against Woman and Girls 2015 Survey.^31 32^ We will also conduct in-depth interviews to explore the woman’s attitudes and perceptions of IPV qualitatively.

### Participant recruitment and timeline

A household census in the study area will record the names and contact details of all women who agree to participate, and we will enter their details into an electronic system. The system will generate for each participant with a unique ID number and quick response code. SCC surveillance workers will then conduct door-to-door visits each month to identify women that have missed two menstrual periods in a row. The woman will then undertake a pregnancy test (using a urine test kit (Excel). We will invite women who test positive for pregnancy to participate in the study with appropriate informed written consent. Based on experience with our pilot study, we anticipate 95% of the mothers will consent. Qualitative and quantitative data will be gathered at the start of the intervention and at endline (online supplemental appendix table 2).

### Allocation of clusters

Our study site has over 1100 villages, which would be adequate to cover the anticipated sample size. Each cluster encompasses two to four villages and consists of ~1000 households and ~4500 population. We will use a fixed randomisation scheme to assign treatments to eligible clusters, with a uniform allocation ratio of treatments, stratified by union. The sample size will consist of 104 clusters, total women (n=2840) allocated to two parallel groups (n=1420) with 20 mother–infant dyads per cluster. Each cluster consists of one to four adjacent villages with a minimum population of 600 households per cluster with 454 villages in our study area for clustering. A subsample of the households from a purposively selected subset of clusters will be chosen for qualitative data.

The intervention and control groups will receive similar maternal and child health and nutrition services from the government, and the critical difference will be the nutrition BCCs with cash transfers on a mobile platform received by women in the intervention arm. The study design will control for potential observed and unobserved confounding factors as there will be an adequate number of clusters randomly allocated to the treatment groups. The geographical separation of clusters will limit the contamination of the intervention arm. We will use STATA V17 software to generate the random allocation sequence. We are unable to mask the treatment arm due to the nature of the intervention.

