### Sample size and power

The sample size for our trial is fixed by the primary hypothesis in the main SCC Trial, which estimated a total sample of 2184 mother–infant pairs from 104 clusters.^12^ We can find no reports of intracluster correlation coefficients (ICCs) for the women’s empowerment indicators we plan to use. Therefore, we estimate that the fixed trial sample size will provide at least 80% power to detect a 20% increase in women’s empowerment, assuming 30% of women are empowered and a high ICC of 0.2. Assuming a lower ICC of 0.05, we will have 90% power to detect a 13% increase in women’s empowerment.

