### Quantitative data analysis

Data analysis will be by intention to treat. The women’s empowerment composite index scores will be categorised as the percentage of women as empowered or disempowered. For each empowerment indicator, individuals are classified as adequate or inadequate based on Pro-WEAI predetermined thresholds. Women are considered empowered if four out of six indicators are adequate. We will also analyse impact of SCC intervention on individual indicators to assess increases or decreases in empowerment as not all indicators will respond or be impacted in the same way.

Analyses will be conducted at the mother–infant dyad level but will be adjusted for the cluster randomisation.^39^ Primary analyses will compare the prevalence of women’s empowerment at the end of the trial using Pearson’s χ^2^ tests and 95% CIs for the group difference, adjusted for clustering and generalised linear mixed models for non-continuous outcomes (eg, logistic mixed models for binary outcomes, for example, percentage of women’s empowerment). Models will include treatment group as a fixed effect, infants as a random effect to account for repeated measurements, and community cluster as a random effect to account for cluster effects. We will also assess if the women’s empowerment level at baseline, age, education, and presence or absence of a mother-in-law in the household modify the empowerment response to the intervention by testing for interactions between the intervention and these factors. STATA will be used for all analyses.

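### Randomisation is stratified by union but the stated analysis has no union term, so reported standard errors will be too large to the extent that empowerment varies between unions

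*Protocol article*

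**What the plan says.** Under Allocation of clusters, the protocol article describes a fixed randomisation scheme for the clusters, "with a uniform allocation ratio of treatments, stratified by union". Union is therefore a design factor that restricts the allocation.

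Under Quantitative data analysis, the comparison of empowerment prevalence at the end of the trial uses a chi-squared test and "95% CIs for the group difference, adjusted for clustering", together with generalised linear mixed models. The model terms are spelled out: "Models will include treatment group as a fixed effect, infants as a random effect to account for repeated measurements". The one remaining term listed is a second random effect, for the cluster. Union is not among these terms. Nor is it among the factors to be tested for interaction with the intervention, which are baseline empowerment, age, education and the presence of a mother-in-law.

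The Sample size and power section does not mention stratification and claims no gain in precision from it. The article gives neither the number of unions nor any between-union variance.

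**The concern.** When arms are balanced within strata, differences between strata largely cancel from the treatment contrast, so the true sampling variance of the treatment effect falls. A model with a cluster random effect and no stratum term cannot see this. It treats differences between unions as ordinary between-cluster variation and carries them into the standard error. The estimate is then more precise than its reported interval says, and the nominal 5% test rejects less often than 5% under the null.

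This matters here for two reasons. The article says that no ICCs could be found for these indicators and allows for one as high as 0.2, which is where the effect is largest. The number of clusters is also fixed by the main trial, so precision cannot be bought with more clusters.

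**Working it through.** **Inputs from the protocol article**
- Sample: the power section "estimated a total sample of 2184 mother–infant pairs from 104 clusters", so m = 2184/104 = 21 per cluster.
- The allocation section gives other figures: "total women (n=2840) allocated to two parallel groups (n=1420) with 20 mother–infant dyads per cluster". These imply m = 20, or 2840/104 = 27.3. The conflict is a separate matter, so all three values of m are tried below.
- Base rate and ICC: "assuming 30% of women are empowered and a high ICC of 0.2"; the lower ICC is 0.05.

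**Assumptions**
- Two-sided 5% level, read from the 95% intervals, since no alpha is stated.
- f, the share of between-cluster variance that lies between unions, is 0.10 to 0.30. It is not in the documents.
- Arms are balanced exactly within each union.

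**Step 1. The plan's own power figures.** With the design effect 1 + (m − 1) × ICC:
- ICC 0.2: 1 + 20 × 0.2 = 5, so 1092/5 = 218.4 effective women per arm. Power for 30% vs 50% is 99.1%.
- ICC 0.05: 1 + 20 × 0.05 = 2, so 1092/2 = 546 per arm. Power for 30% vs 43% is 99.4%.

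The claim of at least 80% holds as a bound, but the stated 90% is not reproduced. Read as relative increases (36% and 33.9%), power is 26.5% and 28.1%. This is also a separate matter. It shows here how far power could depend on a union term at the planned effects.

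**Step 2. Reported against true standard error.** Up to a common factor, the variance of a cluster mean is v = ICC + (1 − ICC)/m. Balance within union removes f × ICC from the true variance of the contrast, while a model without union still reports v. Hence

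ratio = √[ v / (v − f × ICC) ], and true two-sided error = 2 × [1 − Φ(1.96 × ratio)].

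With m = 21:

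| ICC | v | f | v − f × ICC | Ratio | True two-sided error |
|---|---|---|---|---|---|
| 0.2 | 0.2381 | 0 | 0.2381 | 1.000 | 5.0% |
| 0.2 | 0.2381 | 0.10 | 0.2181 | 1.045 | 4.1% |
| 0.2 | 0.2381 | 0.30 | 0.1781 | 1.156 | 2.3% |
| 0.05 | 0.0952 | 0 | 0.0952 | 1.000 | 5.0% |
| 0.05 | 0.0952 | 0.10 | 0.0902 | 1.027 | 4.4% |
| 0.05 | 0.0952 | 0.30 | 0.0802 | 1.089 | 3.3% |

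The choice of m hardly matters. For f = 0.10 to 0.30, m = 20 gives 1.045–1.155 (ICC 0.2) and 1.027–1.087 (ICC 0.05); m = 27.3 gives 1.047–1.164 and 1.031–1.102.

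**Step 3. Check by simulation.** A linear cluster-level analysis was simulated with 104 clusters, m = 21, ICC 0.2, f = 0.25, an assumed 17 unions and 4000 runs per setting:

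| | Simple randomisation | Stratified, no union term | Stratified, union term |
|---|---|---|---|
| True SD of the estimate | about 0.047 | about 0.041 | not tabulated |
| Mean reported SE | not tabulated | 0.047 | 0.042 |
| Rejection under the null | 5.3% | 2.9% | 5.0% |
| Power for a 12-point effect | 0.72 | 0.74 | 0.80 |

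The simulated error of 2.9% agrees with the formula, which gives a ratio of 1.125 and an error of 2.7% at f = 0.25. At the planned effects read as percentage points (20 and 13), power is about 99% or more with or without the term.

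**The case against.** The strongest objection is that handling of stratification factors is routine content of a statistical analysis plan, which is not shown here, and that the article never says union is excluded. This lowers certainty about what will finally be done. It does not remove the point, because the article names the fixed and random effects and the list leaves out the factor that restricted the randomisation. A later plan that includes union would be adding to this published list.

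The second objection is that the error is in the safe direction, and this stands. Type I error is at or below 5% and there is no false-positive risk.

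The third is that the size rests on an assumed f and a linear approximation, whereas the article plans logistic mixed models. Unions with an odd number of clusters will also not balance exactly. This stands too: the direction is firm, the size is not.

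Three stronger readings are tempting, and the documents support none of them:
- *The stratification achieves nothing without a union term.* It still balances the arms by union, and in the simulation it cut the true SD of the estimate from about 0.047 to 0.041. Only the reported standard error, interval and p-value fail to show this.
- *The standard errors are certainly too large.* That depends on unions differing in empowerment, on which the article gives no information.
- *Planned power is lost.* The power section counts on no gain from stratification, and power at its percentage-point effects is about 99% either way.

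**Conclusion.** The design and the stated analysis do not match, and the direction of the consequence is clear: if unions differ, the reported standard errors overstate the true ones. With an assumed 10–30% of between-cluster variance lying between unions, intervals are about 4–16% too wide at ICC 0.2 and about 3–9% too wide at ICC 0.05. If unions do not differ, the inflation is zero. These figures rest on exact balance within union, a linear cluster-mean approximation and a two-sided 5% level.

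This is a point about efficiency and does not threaten validity. The benefit of correcting it lies in interval width and in power for effects smaller than those planned (0.80 against 0.74 in the simulated example) and for the secondary outcomes, for which no power is stated. It is worth making because the correction costs little.

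**What to change.** In Quantitative data analysis, add union, the randomisation stratum, as a fixed effect in the primary and secondary models. Use a union-stratified form of any cluster-adjusted chi-squared test or confidence interval. If union is left out on purpose, say so and note that the test is then conservative.

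The cost is one degree of freedom per union beyond the first, out of about 104 − 2 = 102 at cluster level. The number of unions is not stated; with the 17 assumed in the simulation it would be 16. For binary outcomes, fix in advance a rule for pooling small unions in case some strata are too sparse for a stable fit. No change to the design, sample or data collection is needed.

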**Methods and analysis:**

We will use a mixed-methods approach, combining statistical analysis of quantitative data from 2840 women in a cluster randomised controlled trial examining the impact of nutrition behaviour change communications (BCCs) and cash transfers on child undernutrition. Pregnant participants will be given a smartphone with a customised app, delivering nutrition BCC messages, and will receive nutrition counselling via a call centre and an unconditional cash transfer. This study is a component of the SCC Trial and will measure women’s empowerment using a composite indicator based on the Project-Level Women’s Empowerment in Agriculture Index, with quantitative data collection at baseline and endline. Thematic analysis of qualitative data, collected through longitudinal interviews with women, husbands and mothers-in-law, will elicit a local understanding of women’s empowerment and the linkages between the intervention and women’s empowerment outcomes. This paper describes the study protocol to evaluate women’s empowerment in a nutrition-specific and sensitive intervention using internationally validated, innovative tools and will help fill the evidence gap on pathways of impact, highlighting areas to target for future programming.

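### The stated 104 clusters, 20 dyads per cluster and 2840 women do not multiply, and 2840 is never reconciled with the 2184 used in the power section

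*Protocol article*

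**What the plan says.** The protocol article gives its sample size in four places.

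- **Allocation of clusters:** "The sample size will consist of 104 clusters, total women (n=2840) allocated to two parallel groups (n=1420) with 20 mother–infant dyads per cluster". Allocation is at a uniform ratio, which with two arms means 52 clusters per arm.
- **Sample size and power:** the size is said to be fixed by the main trial, which "estimated a total sample of 2184 mother–infant pairs from 104 clusters". The power statements rest on this fixed size.
- **Study design:** the trial will recruit pregnant women, with "follow-up over 24 months of an expected 2840 mother–child dyad".
- **Abstract, Methods and analysis:** the study is described as "combining statistical analysis of quantitative data from 2840 women in a cluster randomised controlled trial".

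The Allocation of clusters section also describes the cluster twice: "Each cluster encompasses two to four villages and consists of ~1000 households and ~4500 population" and, a few sentences later, "Each cluster consists of one to four adjacent villages with a minimum population of 600 households per cluster with 454 villages" in the study area for clustering.

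No attrition allowance is given. The only related rate is the 95% of mothers expected to consent (Participant recruitment and timeline), which applies before enrolment.

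**The concern.** One sentence fixes three quantities, any two of which determine the third, and they disagree. The next section then gives another total for the same number of clusters. The same 104 clusters therefore carry three cluster sizes: 20 (printed), 21 (implied by 2184) and about 27.3 (implied by 2840).

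Several things depend on these figures. The number of women to enrol and the number expected per cluster are basic design facts. The monitoring board is asked to judge data against recruitment and retention goals, and retention cannot be judged if 2840 might be either the enrolled or the analysed number. The eventual report will also need a planned denominator to set against the achieved one. In a cluster trial the number of clusters and their size both enter the power calculation, so it has to be checked whether the discrepancy carries through to power.

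**Working it through.** **Inputs.** From Allocation of clusters: 104 clusters, 2840 women, 1420 per arm, 20 dyads per cluster, equal allocation. From Sample size and power: 2184 pairs, 104 clusters, 30% empowered, intracluster correlation (ICC) 0.2 or 0.05, increases of 20% and 13%. Assumed, because the article does not state it: two-sided alpha of 0.05.

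**Step 1. Which figures reproduce.**

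- 2 x 1420 = 2840. The total and the per-arm number agree.
- 2184 / 104 = 21.0. The power section's total is consistent with a whole-number cluster size.
- 104 x 20 = 2080, or 52 x 20 = 1040 per arm. This is neither 2840 nor 2184.
- 2840 / 104 = 1420 / 52 = 27.3 per cluster, not 20.

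**Step 2. Whether a stated rate links the totals.**

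- 2840 to 2184: 1 - 2184/2840 = 23.1% loss. Expressed as an uplift, 2184 x 1.30 = 2839.
- 2840 to 2080: 1 - 2080/2840 = 26.8% loss.
- 2080 to 2184: 2080 x 1.05 = 2184.
- The 95% consent rate: 2840 x 0.95 = 2698 and 2184 / 0.95 = 2299, neither of which is a stated figure. 2080 / 0.95 = 2189 comes near 2184 but does not equal it. In any case consent acts before enrolment and cannot explain loss afterwards.

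None of the 5%, 23%, 27% or 30% allowances appears in the article.

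**Step 3. Effect on power with 104 clusters.** Effective n per arm = 52m / [1 + (m - 1) x ICC], where m is the number of women per cluster. At ICC 0.2:

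- m = 20: 1040 / 4.8 = 216.7
- m = 21: 1092 / 5.0 = 218.4
- m = 27.3: 1420 / 6.26 = 226.8

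A two-proportion normal approximation then gives:

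| Total (per cluster) | Effective n per arm, ICC 0.2 | Power, 30% vs 50%, ICC 0.2 | Power, 30% vs 43%, ICC 0.05 | Difference detectable with 80% power, ICC 0.2 |
|---|---|---|---|---|
| 2080 (20) | 217 | 99.0% | 99.3% | 12.9 points |
| 2184 (21) | 218 | 99.1% | 99.4% | 12.9 points |
| 2840 (27.3) | 227 | 99.3% | 99.7% | 12.6 points |

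Here the 20% and 13% increases are read as absolute. Read as relative (30% to 36%, and 30% to 33.9%), power is 26% to 27% and 28% to 31% across the same three totals. On either reading, changing the total moves power by about 3 percentage points at most.

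**Step 4. The cluster description.** Two to four villages and one to four villages cannot both be the rule. About 1000 households as a typical size is compatible with a minimum of 600. Over 1100 villages in the study site and 454 available for clustering may be counts of different areas.

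**The case against.** The strongest defence is that 2840 is the number enrolled and 2184 the number evaluable. Women enter at 90 days' gestation or less and are followed until the child is 18 months old, so loss is to be expected, and a 30% uplift on 2184 lands almost exactly on 2840. The derivation may well be in the separate main-trial protocol, which is not at hand. This reading is plausible and may be what was meant. It does not rescue the text, however. No loss rate is printed, the Study design section calls the 2840 mother–child dyads under follow-up, and the abstract calls them women whose data are analysed. Even if 20 meant dyads retained, 20 x 104 gives 2080 and not 2184.

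Some stronger inferences should be resisted.

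- **That the sample size or power basis is undefined.** It is not. Only two totals are printed; 2080 is a product of the printed cluster count and cluster size. The total of 2840 is used consistently in three places, and the power section names 2184 as its basis. The figures are unreconciled rather than absent.
- **That 2840 at 20 per cluster implies 142 clusters, and so overstated power.** The arithmetic is right (2840 / 20 = 142), but both statements of the cluster count say 104, so nothing in the article supports a 142-cluster design.
- **That field work lacks a quota.** The recruitment section describes monthly surveillance and an invitation to women who test positive. It sets no fixed quota.
- **That the household and village counts contradict each other.** As shown above, they can be read as compatible.

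**Conclusion.** The point holds as an arithmetical contradiction in the stated sample size. The sentence in Allocation of clusters is impossible: its total is 37% above what its own cluster count and cluster size give (2840/2080 = 1.37), and 30% above the power section's total for the same clusters (2840/2184 = 1.30). The cluster size is the least settled figure.

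The consequence for inference is small. With 104 clusters and an ICC of 0.2, the effective sample size is 217 to 227 per arm whichever total is meant, and the detectable difference changes by about 0.3 points. This rests on equal allocation of clusters, equal cluster sizes and two-sided alpha of 0.05. The damage is to the stated sample size, the per-cluster target and the denominator against which recruitment and retention will be judged.

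The power section's pairing of 80% with a 20% increase and 90% with a 13% increase is a separate matter. Choosing one total would not settle it.

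**What to change.** State one consistent set of numbers in the abstract, Study design, Allocation of clusters, and Sample size and power: 104 clusters (52 per arm under equal allocation), women per cluster, women enrolled, and women expected at endline with the assumed loss. Two versions are consistent with the article's other figures:

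- 2184 throughout, as 104 x 21, with 1092 per arm; or
- 2840 enrolled (about 27 per cluster, 1420 per arm), with about 23% loss leaving 2184 evaluable (21 per cluster). The abstract should then no longer describe 2840 as the women analysed.

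In either case the figure of 20 per cluster has to be corrected. State the power on the chosen set, and settle whether a cluster comprises one to four or two to four villages.

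The cost is a text correction and a rerun of a short calculation. It needs no extra participants or clusters, although the headline sample becomes smaller if 2184 is the intended total.
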